## Definitions

An **Adverse Event** (AE) is any untoward medical event affecting a clinical trial participant. An AE can be any unfavourable and unintended sign (including an abnormal laboratory finding), symptom, or disease (new or exacerbated) temporally associated with the use of a medicinal product, whether or not considered related to the intervention. Each initial AE will be considered for severity, causality or expectedness by the Investigator and may be reclassified as a serious event or reaction based on prevailing circumstances.

An **Adverse Reaction** (AR) is where it is suspected that an AE has been caused by a reaction to acupuncture

A **Serious Adverse Event** (SAE) is any untoward event that occurs at any dose which:

- results in death;
- is life threatening (i.e. the subject was at risk of death at the time of the event; it does not refer to an event which hypothetically might have caused death if it were more severe);
- requires hospitalisation or prolongation of existing hospitalisation;
- results in persistent or significant disability or incapacity;
- is a congenital anomaly or birth defect and/or;
- is considered serious by the Investigator.

Note: Hospitalisations for treatment planned prior to randomisation and hospitalisation for elective treatment of a pre-existing condition will not be considered as an AE. Complications occurring during such hospitalisation will be AEs.

A **Serious Adverse Reaction** (SAR) is an SAE which is causally related to acupuncture. A **Suspected Unexpected Serious Adverse Reaction** (SUSAR) is any SAE which is and which is suspected to be related to the Investigational Product.

## Detecting AEs and SAEs

All AEs and SAEs must be recorded from the time a participant consents to join the study until the last study visit.

The Investigator, treating acupuncturist and research assistant will monitor each subject for Adverse Events during the study. All Adverse Events reported between consent and final follow-up will be recorded in the AE form. The Investigator or designee will ask the subject non-leading questions in an effort to detect Adverse Events e.g.:

“How are you feeling?”

or

“Since you were last asked, have you felt unwell or different from usual?”

In addition, subjects should be encouraged to spontaneously report any unusual feelings or sensations.

Participants should also be asked if they have been admitted to hospital, had any accidents, used any new medicines or changed concomitant medication regimens. If there is any doubt as to whether a clinical observation is an AE, the event should be recorded.

## Managing potential risks

Most serious adverse events that arise from acupuncture treatment will be avoided in this trial due to the application of exclusion criteria and the choice of acupoint location and type of needles. Pneumothorax and cardiac tamponade are highly unlikely as no points on the thorax will be used. Hepatitis and other blood borne viruses are unlikely to be contracted by the participant as only sterile disposable needles will be used. Compartment syndrome is unlikely as no anti-coagulated participants will be accepted into the trial. Endocarditis occurs in participants with prosthetic valves, and these participants are excluded from the trial. Neurological damage and deep venous thrombosis are possible, though rare, and measures to avoid these during the trial include careful acupoint location and avoidance of vigorous stimulation of the needle.

A systematic review of adverse events in auricular acupuncture trials found relatively few reports of adverse events, and no reports of serious adverse events. The adverse events for auricular acupuncture (total of 1753 participants monitored) included:

- pain and tenderness (7.6%)
- minor bleeding (1.4%) which resolved immediately with pressure
- Dizziness (2.9%) which resolved spontaneously
- mild inflammation (0.1%)
- discomfort (1.4%)

Adverse events for auricular electro-acupuncture (total of 203 participants monitored) included:

- discomfort (1%)
- pain (0.5%)

In our partner's experience with the Neurova during an uncontrolled clinical trial (16 participants) there were no adverse events relating to pain, inflammation or bleeding. One participant experienced discomfort.

There have been seven published case reports of perichondritis after auricular acupuncture {Baltimore, 1976 #4216;Davis, 1985 #4214;Gilbert, 1987 #4212;Johansen, 1990 #4211;Sorensen, 1990 #4210}. All occurred before 1990. The lack of reports of perichondritis in the past 27 years may represent increased awareness of the importance of adequate precautions to minimise the risk of infection. In this trial, the concha of the ear is to be cleaned thoroughly with an alcohol swab prior to insertion of the sterile needles. Perpendicular insertion into the cartilage of the ear is to be avoided, instead the insertion of the small needles is safest when done obliquely. Participants are instructed to seek medical advice immediately upon any signs of infection such as redness, pain, heat, purulence or swelling.

The auricular ear-acupuncture stimulation device has not been trialled in pregnancy. Due to this lack of safety data, any woman intending on falling pregnant during the intervention period is to be excluded. Women are asked to avoid falling pregnant, and cease using the ear acupuncture device should they become pregnant.

## Managing adverse outcomes

Participants will be informed of the possible adverse outcomes arising from acupuncture treatment, including the “minor” outcomes such as fainting and pain around needle insertion sites. Practitioners will receive “refresher” training on dealing with common adverse events during treatment, and information on prevention and treatment of adverse events are also found in the Practitioner Training Manual.

Any adverse outcomes occurring during treatment will be dealt with as appropriate by the treating practitioner as below:

- Bleeding or bruising: gentle, firm pressure is applied with a cotton ball for at least 5 minutes. If bruising is large, a cold pack may be applied.
- Drowsiness: participants are to remain in treatment or waiting room until drowsiness passes, unless they are being driven home by somebody else.
- Pain during treatment – The needle is withdrawn slightly if pain persists; if pain does not improve and the participant is too uncomfortable, the needle is withdrawn completely.
- Pain after needle is removed – if there is no bruise/haematoma, the area is to be gently massaged.
- Syncope (fainting) – all needles are removed; participants to be laid flat (no pillow under the head) and with raised legs. Breathing and pulse rate are to be assessed every two minutes. If the situation is normal or improving, the participant is allowed to rest or recover. If the situation deteriorates, strategies such as massaging GV20 and letting other people know the situation and asking for their help. An ambulance should be called if needed.
- Bent needle: the needle is withdrawn slowly if possible (participant may need to return to original position)
- Needle breakage: the needle is removed with a pair of artery forceps if the residual needle is above the skin. If the needle is below skin level, the practitioner will mark and stabilise the area and refer to a hospital or GP for surgical removal. Dizziness: the participant is allowed to lie down until dizziness passes.
- Fatigue after acupuncture: gentler manipulation will be used for the next session.

## Recording AEs AND SAEs

Depending on severity, when an AE/SAE occurs, it is the responsibility of the Investigator to review all documentation related to the event. The Investigator should then record all relevant information in the AE form.

Information to be collected includes dose, type of event, onset date, Investigator assessment of severity and causality, date of resolution as well as treatment required, investigations needed and outcome.

## Evaluation OF AEs AND SAEs

Seriousness, causality, severity and expectedness should be evaluated as though the participant is taking active drug. Cases that are considered serious, possibly, probably or definitely related to drug and unexpected (i.e. SUSARs) are likely to be unblinded.

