# Study Design

This is a prospective open-label parallel randomised controlled feasibility study taking place over a 12 week intervention period.

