# Study Population

## Number of Participants

We aim to analyse 30 participants by the end of treatment. Allowing for a 25% dropout rate which has been reported in similar studies, we will randomise 39 women (13 to real acupuncture, 13 to AEA and 13 to lifestyle alone).

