#### Blinding

Investigators (outcome assessors and investigators involved in statistical analysis) are blinded to treatment allocation but treating acupuncturists and participants are not.

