### Quality assurance

As part of monitoring of treatment fidelity and quality assurance, practitioners are requested to take a digital photo of the first insertion of the Neurova that they perform, to be verified by the Chief Investigator and by NESI Corp (the manufacturers). This photo will not contain any identifying features such as facial features. The photo will be labelled with the participant ID number and date of treatment only, and emailed to [name], who will then store the photograph on a secure University cloud-based server.

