### Assessment of Causality

The Investigator must make an assessment of whether the AE/SAE is likely to be related to treatment according to the following definitions:

**Unrelated**: where an event is not considered to be related to the study drug.

**Possibly**: although a relationship to the study drug cannot be completely ruled out, the nature of the event, the underlying disease, concomitant medication or temporal relationship make other explanations possible.

**Probably**: the temporal relationship and absence of a more likely explanation suggest the event could be related to the study drug.

**Definitely**: The known effects of the study drug or its therapeutic class, or based on challenge testing, suggest that study drug is the most likely cause.

All AEs/SAEs judged as having a reasonable suspected causal relationship (e.g. possibly, probably, definitely) to the study drug will be considered as ARs/SARs. All AEs/SAEs judged as being related (e.g. possibly, probably, definitely) to an interaction between the study drug and another drug will also be considered to be ARs/SAR.

Alternative causes such as natural history of the underlying disease, concomitant therapy, other risk factors and the temporal relationship of the event to the treatment should be considered. The blind should not be broken for the purpose of making this assessment.

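### Adverse-event causality and expectedness follow blinded drug-trial rules that contradict the open-label design, the two different needling arms and the coaching-only control

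*Protocol*

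**What the plan says.** Protocol section 10.6 (Evaluation of AEs and SAEs) sets the rule for every adverse event: "Seriousness, causality, severity and expectedness should be evaluated as though the participant is taking active drug". It adds that serious, related and unexpected cases will probably be unblinded. Section 10.6.2 (Assessment of Causality) grades each event against a study drug, counts a rating of possibly related as enough for an adverse reaction, and closes: "The blind should not be broken for the purpose of making this assessment".

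Other sections describe a different trial:

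- Section 3 (Study Design): "This is a prospective open-label parallel randomised controlled feasibility study taking place over a 12 week intervention period".
- Section 5.5.1 (Blinding): "Investigators (outcome assessors and investigators involved in statistical analysis) are blinded to treatment allocation but treating acupuncturists and participants are not".
- Section 6.3: the control arm receives the lifestyle intervention only.
- Section 10.1 (Definitions): an adverse reaction "is where it is suspected that an AE has been caused by a reaction to acupuncture".

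Section 2.2.1 lists safety within the primary endpoint.

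**The concern.** In a placebo-controlled drug trial, assuming active treatment is a sensible convention. There is one active product, the assessor does not know who received it, and assuming exposure is the cautious choice. None of those conditions holds here. There is no drug and no sham, there are two active treatments, and the third arm receives no trial needling.

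Two things are at stake. First, the meaning of an adverse reaction: a woman on coaching alone cannot react to trial needling, yet her event is to be judged as if she were exposed. Second, expectedness, and with it SUSAR status: the answer depends on which needling treatment is assumed, and the protocol does not say. This is a stated rule for what the Investigator records on the adverse-event form, so a later analysis document would not normally repair it.

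**Working it through.** The protocol gives no figure on this point to reproduce. The check is a comparison of sections, followed by an illustration of scale.

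**1. What is the active treatment?** Section 10.1 ties adverse reactions to acupuncture and SUSARs to an Investigational Product. Section 10.6 refers to an active drug and section 10.6.2 to a study drug. The synopsis lists two investigational therapies, each of which includes coaching. No section says which one stands in for the drug.

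**2. Are the two needling treatments interchangeable for this purpose?** No. Body acupuncture uses at least ten needles, retained for 30 minutes (6.1.2). AEA uses three needles in the concha of one ear with a device, retained for up to 96 hours (6.2.2). Section 10.3 discusses perichondritis for auricular needling only. Deep venous thrombosis and neurological damage appear in its general acupuncture paragraph and not in its auricular lists. The same event can therefore be expected under one assumption and unexpected under the other. Section 10.6.4 refers only to knowledge of the reaction and names no reference list.

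**3. Does unblinding resolve it?** No. Section 10.6 foresees unblinding for cases already judged unexpected, but expectedness cannot be judged until the treatment is known or assumed.

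**4. Is the causality assessor blinded?** The protocol does not say. Section 5.5.1 blinds outcome assessors and analysts. Section 10.6.2 gives causality to the Investigator without saying whether that person is one of them. Section 10.5 has the Investigator review all documentation on the event and lists dose among the items collected. Events are gathered partly by treating acupuncturists, who are unblinded, and by the research assistant (10.2), who opens the allocation envelope (5.5.1).

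**5. Scale of possible misclassification in the control arm.** Inputs: 13 women per arm, 39 in all (4.1), so 13/39 = 33% receive no trial needling. Let q be the proportion of control women with a background event. The protocol gives no value for q, so 5% to 30% is an assumption. The worst case takes every such woman as rated possibly related.

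- Expected number misclassified = 13 × q
- Chance of at least one = 1 − (1 − q)^13

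| q (assumed) | Expected women | Chance of at least one |
|---|---|---|
| 5% | 0.65 | 49% |
| 10% | 1.3 | 75% |
| 20% | 2.6 | 95% |
| 30% | 3.9 | 99% |

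Judged against the treatment received, the count of trial-acupuncture reactions in this arm is 0 under section 10.1.

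**The case against.** The strongest reply is that a sensible Investigator would not produce these errors. Section 10.6.2 keeps an unrelated category, asks for a reasonable suspicion of causation, and requires other explanations, including timing relative to treatment, to be weighed. This stands, and it is why the table is a worst case and not a forecast.

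A second reply is that the trial is not wholly unblinded, since section 5.5.1 blinds outcome assessors and analysts. This also stands: a masked causality review is possible on paper. What the protocol fails to do is assign that review to a blinded person or protect the blind.

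A reader might infer several stronger claims that the documents do not support:

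- *That adverse-reaction counts by arm will be wrong.* Misclassification is possible, not certain, and the protocol does not say that such counts will be reported by arm.
- *That needling risk will be understated.* A rule applied alike to all three arms admits background events in all of them, so the direction of any effect on a between-arm difference is not established.
- *That the device photographs destroy the blind.* Section 6.2 says "The photo will be labelled with the participant ID number and date of treatment only", but it asks only for each practitioner's first insertion, and the stated minimum is six practitioners. Most allocations need not be revealed this way.
- *That one misclassified control woman gives the size of the error.* 1/13 = 7.7 percentage points is simply the weight of one woman in an arm of 13. Its closeness to the 7.6% quoted for pain and tenderness in section 10.3 is coincidence; the auricular electro-acupuncture rates there are 1% and 0.5%.
- *That safety will decide which arm goes forward.* The summary says only that the data will inform a larger trial.

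**Conclusion.** The contradiction is real and should be corrected. Sections 10.6 and 10.6.2 cannot be applied as written alongside sections 3, 5.5.1, 6.3 and 10.1. Followed literally, they allow acupuncture reactions to be recorded in women who had no trial needling, and they leave expectedness undefined between body acupuncture and AEA.

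No figure in the protocol is shown to be wrong. Under the assumed 5% to 30% background rate and the worst-case rating, 0.65 to 3.9 of 13 control women would be misclassified on average; careful use of the unrelated category would reduce this, possibly to none. The implied zero refers to trial needling only, because section 6.4 allows complementary co-interventions. All-cause adverse-event counts do not change. The size and direction of any between-arm bias cannot be determined from the protocol.

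**What to change.** Reconcile sections 10.1, 10.6, 10.6.2 and 10.6.4 with sections 3, 5.5.1 and 6.3:

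- Remove the wording on active drug, study drug, keeping the blind and unblinding.
- State who judges causality and what that person knows of the allocation.
- Judge causality and expectedness against the intervention actually received: body acupuncture, AEA or coaching alone.
- Give a separate expectedness reference for each needling arm. Section 10.3 can start the AEA list. It gives event rates only for auricular treatment, and section 10.4 is a management list, so the body-acupuncture reference has to be written.
- Report all-cause adverse events by arm as the between-arm safety comparison, and report adverse reactions separately for body acupuncture and AEA.

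The cost is replacement wording, two short reference lists and a small change to the adverse-event form. There is one real downside. Relatedness is then judged with knowledge of the arm, so reaction counts in the needling arms may include background events. They should not be contrasted with a control count that is zero by definition, which is why the between-arm comparison should rest on all-cause events.

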### Assessment of Seriousness

The Investigator should make an assessment of seriousness as defined in 10.1.

### Assessment of Causality

The Investigator must make an assessment of whether the AE/SAE is likely to be related to treatment according to the following definitions:

**Unrelated**: where an event is not considered to be related to the study drug.

**Possibly**: although a relationship to the study drug cannot be completely ruled out, the nature of the event, the underlying disease, concomitant medication or temporal relationship make other explanations possible.

**Probably**: the temporal relationship and absence of a more likely explanation suggest the event could be related to the study drug.

**Definitely**: The known effects of the study drug or its therapeutic class, or based on challenge testing, suggest that study drug is the most likely cause.

All AEs/SAEs judged as having a reasonable suspected causal relationship (e.g. possibly, probably, definitely) to the study drug will be considered as ARs/SARs. All AEs/SAEs judged as being related (e.g. possibly, probably, definitely) to an interaction between the study drug and another drug will also be considered to be ARs/SAR.

Alternative causes such as natural history of the underlying disease, concomitant therapy, other risk factors and the temporal relationship of the event to the treatment should be considered. The blind should not be broken for the purpose of making this assessment.

### Assessment of Severity

The Investigator should make an assessment of severity for each AE/SAE and record this on the CRF according to one of the following categories:

**Mild**: an event that is easily tolerated by the participant, causing minimal discomfort and not interfering with every day activities.

**Moderate**: an event that is sufficiently discomforting to interfere with normal everyday activities.

**Severe**: an event that prevents normal everyday activities.

Note: the term ‘severe’, used to describe the intensity, should not be confused with ‘serious’ which is a regulatory definition based on participant/event outcome or action criteria. For example, a headache may be severe but not serious, while a minor stroke is serious but may not be severe.

### Assessment of Expectedness

If an event is judged to be an AR/SAR, the evaluation of expectedness should be made based on knowledge of the reaction.

## Reporting of SAEs/SARs/SUSARs

Once the Investigator becomes aware that an SAE has occurred in a study participant, they must report the information to the Sponsor within 24 hours of becoming aware of the event. The SAE form must be completed as thoroughly as possible with all available details of the event, signed by the Investigator or designee. If all the required information is not available at the time of reporting, the Investigator must ensure that any missing information is provided as soon as this becomes available. It should be indicated on the report that this information is follow-up information of a previously reported event.

The SAE report must provide an assessment of causality and expectedness at the time of the initial report to the Sponsor according to Sections 10.4.2 Assessment of Causality and 10.4.4 Assessment of Expectedness.

## Follow up Procedures

After initially recording an AE or recording and reporting an SAE, the Investigator is required to follow each participant until the AE/SAE resolves or is considered stable by both the Investigator and Sponsor if ongoing at the final follow-up visit. Follow up information for an SAE should be reported to the Sponsor.

# Good Clinical Practice Module

## Ethical Conduct of the Study

This study will be carried out according to the Declaration of Helsinki, the NHMRC National Statement on Ethical Conduct in Research Involving Humans (1999) and the Notes for Guidance on Good Clinical Practice as adopted by the Australian Therapeutic Goods Administration (2000) (CPMP/ICH/135/95) and the ICH GCP Guidelines.

The protocol and related documents will be submitted for review by the Human Research Ethics Committee (HREC) and written approval received before the study can commence.

## Investigator Responsibilities

The Investigator is responsible for the overall conduct of the study at the site and compliance with the protocol and any protocol amendments. In accordance with the principles of GCP, the following areas listed in this section are also the responsibility of the Investigator. Responsibilities may be delegated to an appropriate member of study site staff. Delegated tasks must be documented on a Delegation Log and signed by all those named on the list.

